### **3. Patients**

#### **Included will be:**

- all comers, 24 hours a day, 7 days a week, irrespective of indication for PCI
- in need of large ( $\geq 3.0$  mm stents only) native vessel stenting

#### **Excluded will be patients with**

- in-Stent Restenosis or in-Stent Thrombosis
- bypass graft disease to be stented
- main stem disease to be stented
- cardiogenic shock by clinical assessment (signs of organ hypoperfusion)
- planned surgery within the next 12 months
- oral anticoagulation needed (artificial heart valves, atrial fibrillation) or chronic haemorrhagic diathesis
- active bleeding disorders
- index-PCI = planned PCI of additional lesion
- no FU expected/possible
- History of stroke or TIA (contrindication for prasugrel)
- known severe hypersensitivity reaction to ASS and/or Prasugrel
- no compliance expected / no informed consent given
- enrolled in another study

#### 4. Study design

BASKET-PROVE II will be a prospective randomized open-label multicenter trial

Randomization will be 2:1 for DES to BMS. The DES group will be sub-randomized 1:1 for XienceV® to Nobori®.

All patients will receive a loading dose of Aspirin (300-500mg) and of Prasugrel (60mg) initially, followed by a maintenance dose of Aspirin 100mg and Prasugrel 10mg daily for 1 month after BMS in elective patients and 12 month after DES implantation and after BMS implantation in patients with ACS as currently recommended. All other treatments will be given according to current guidelines and patient needs (based on local treating physicians prescriptions, see point 6)

[figure not shown]

Patients without emergency intervention will be included in the study after giving written informed consent. Since BASKET-PROVE II is an all-comer, real-world trial, the quality of the trial strongly depends on inclusion of not only elective, but also emergency patients with acute coronary syndrome and myocardial infarction. Since

these patients commonly suffer from acute chest pain and dyspnea and since every minute of time delay would adversely affect prognosis, it is ethically not acceptable to postpone the intervention to obtain written informed consent prior to study inclusion (in accordance with the Swiss federal law on drugs and medical devices [Heilmittelgesetz], Art. 56). Thus, as soon as coronary intervention is planned and the patient fulfils study entry criteria, the patient will be informed about the trial and asked for oral consent by the operator in charge. This will be done in parallel to preparation of material for coronary intervention, guaranteeing no time delay by inclusion of the patient in the study. Oral consent will be documented on the informed consent form by a second medical person not being involved in the trial. Only with oral consent, the patient will be included in the study and will have to give the definitive written informed consent after the PCI-procedure. Baseline PCI consists of the index procedure and of all planned PCI thereafter ("two step").

## 5. Follow-up

- Follow-up will be clinical with no “routine” follow-up angiography allowed (follow-up angiography only for relevant new symptoms!)

After 24 , 36 and 60 months a structured questionnaire will be sent to all study patients regarding clinical events (1st, 2nd endpoints) as well as drugs used. In addition, quality of life will be assessed using the self-administered EQ-5D questionnaire, which consists of a self classifier and a visual analogue scale, at baseline and after 24, 36 and 60 months (26,27). All events will be documented based on hospital and/or private physician charts/discharge letters.

- A separate registry will be conducted including all patients treated with PCI during the time of randomisation but not included in the main trial.

## 6. Concomitant Therapy

Concomitant therapy will be

- Aspirin \* 100 mg/day throughout
- statin throughout
- Prasugrel \* :

*Dosage:*                    -10 mg/day in patients  $\leq 75$  years and body weight  $\geq 60$ kg  
                                     - 5 mg/day in patients  $> 75$  years or body weight  $< 60$ kg

*Duration:*                - 12 months after DES or after BMS in patients with ACS

- 1 month after BMS in elective cases

*Loading dose:* - 60mg

*If loaded with*

*Clopidogrel:* - additional loading with Prasugrel \*\*

- other treatments as clinically indicated

(\*after appropriate loading dosages if indicated)

(\*\*: Reasons for additional loading dose with Prasugrel:

- Same and only mode of action for both drugs at the site of the platelet (irreversible block of P2Y12 - ADP-receptor
- Concentration of active metabolite after loading dose 12 times lower with Clopidogrel compared to Prasugrel
- If no additional loading dose: different levels of platelet inhibition for patients with Clopidogrel and Prasugrel in the early phase
- With additional loading dose: same level of platelet inhibition for all patients in the early phase)

## **7. Treatment of In-Stent-Restenosis:**

In-Stent Restenosis in XienceV®: Treatment with Nobori®

In-Stent-Restesnosis in Nobori®: Treatment with XienceV®

In-Stent Restenosis in PROKinetic Energy®: Treatment with XienceV®

## 8. End-point definitions

1°end-point = freedom of combination of

- cardiac death (all death not clearly of extra cardiac origin)
- documented non-fatal MI (according to the current ESC-guidelines (28))

after 24 months.

2°end-points =

- non-MI related TVR
- major adverse cardiac events (MACE) = 1°end-point events + non-MI related TVR
- 1° end-point events up to 18 months (for comparison with BASKET and BASKET-LATE)
- stent thrombosis according to the ARC-definitions (29)
- components of the 1°end-points
- non-cardiac death, total death
- major non-CABG bleeding (need for surgery, blood transfusions, cerebral haemorrhages) during dual antiplatelet therapy (up to twelve months) – “net clinical benefit” = 1°end-point + bleeding.
- long-term follow-up after 36 and 60 months
- subgroups with
  - diabetes
  - acute coronary syndrome
  - ST-elevation MI
  - need for GP IIb/IIIa inhibitors
  - lesions >25 mm

End-points will be adjudicated by an independent Critical Events Committee (CEC) blinded to the stent type used.

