#### **Endpoints:**

- 1° end-point = freedom of combination of cardiac death (all death not clearly of extra cardiac origin and documented non-fatal MI after 24 months).
- 2° end-points = non-MI related TVR; MACE = 1° end-point events + non-MI related TVR; 1° end-point events up to 18 months (for comparison with BASKET and BASKET-LATE); stent thrombosis according to the ARC-definitions; components of the 1° end-points; non-cardiac death (total death); major non-CABG bleeding (need for surgery, blood transfusions, cerebral haemorrhages) during dual antiplatelet therapy (up to twelve months); “net clinical benefit” = 1° end-point + bleeding; long-term follow-up after 36 and 60 months; subgroups with diabetes, acute coronary syndrome, ST-elevation MI, need for GP IIb/IIIa inhibitors, lesions >25 mm.
- End-points will be adjudicated by an independent Critical Events Committee (CEC) blinded to the stent type used.

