## 2. AIMS

These recent findings and analyses are the basis for two relevant questions which will be addressed prospectively in BASKET-PROVE II.

The primary aim will be:

To assess and compare the 24 month safety (cardiac death/MI) of a new type of BMS with new types of DES in patients at low risk of restenosis, i.e. receiving stents of  $\geq 3,0$ mm diameter only, on the background of contemporary antiplatelet therapy.

The new BMS, with thin cobalt-chromium struts and a biocompatible coating (Prokinetik®), will be compared (in a 1:2 randomisation) to two new DES:

- the most widely used 2nd generation DES with a durable polymer and a low dose - limus drug (XienceV®), which was already used in BASKET-PROVE ),
- a DES with a biodegradable polymer and a -limus drug (biolimus) (Nobori®)

The antiplatelet regime will be Aspirin 100mg and Prasugrel 10mg daily for all patients. Based on current recommendations, this will be given for 1 month after BMS in stable patients and for 12 months after DES implantation and after BMS implantation in patients with ACS.

The secondary aims will be:

- A. To compare the efficacy of BMS vs. DES and then the combined endpoint of safety and efficacy of the primary comparison (BMS vs. DES)
- B. To compare safety and efficacy of each of the new DES to that of the BMS, i.e. XienceV® vs Prokinetik® and Nobori® vs Prokinetik® (both, randomized 1:1)
- C. To compare safety and efficacy of the two new DES, i.e. XienceV® vs. Nobori®

There will be also the possibility to compare findings from BASKET-PROVE II with those of the predecessor study BASKET-PROVE. This will have the following additional secondary aims:

D. To compare safety and efficacy of the earlier BMS strategy (Vision® stent with 12 month clopidogrel), as a historical control, with the new BMS strategy (Prokinetik® stent with 1 month Prasugrel in elective patients and 12 months in patients with ACS)

E. To compare safety and efficacy of the the XienceV® stent in similar patient groups (same indications/exclusions, similar sample size) receiving an antiplatelet therapy of 12 month Clopidogrel (BASKET-PROVE) vs. those receiving 12 month Prasugrel (BASKET-PROVE II) in a "historical" control analysis, evaluating also bleeding rates and "net clinical benefit"

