#### 4 Reporting AEs

AEs will be collected for all patients. AEs will be collected for all patients from first dose of protocol treatment until 30 days after the last dose of treatment with a protocol IMP.

Information about AEs, whether volunteered by the patient, discovered by the investigator questioning or detected through physical examination, laboratory test or other investigation will be collected and recorded in the study files.

If requested, details of all AEs will be made available after completion of the study.

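### Major bleeding is counted only while on dual antiplatelet therapy, so stable patients in the BMS versus DES comparisons are counted for 1 or 12 months depending on arm, and net clinical benefit inherits this

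*Protocol*

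**What the plan says.** Section 8 lists among the secondary endpoints "major non-CABG bleeding (need for surgery, blood transfusions, cerebral haemorrhages) during dual antiplatelet therapy (up to twelve months"), followed by "net clinical benefit” = 1°end-point + bleeding". The synopsis, under Endpoints, uses the same window: "during dual antiplatelet therapy (up to twelve months").

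The length of the therapy is set in section 6. Prasugrel runs "12 months after DES or after BMS in patients with ACS" and "1 month after BMS in elective cases". Sections 2 and 4 agree. Aspirin continues for the whole study, so dual therapy ends when prasugrel ends.

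The primary endpoint, the other component of net clinical benefit, is assessed at 24 months in every arm. Section 10 plans Fisher's exact test for proportions in DES versus BMS, plus Kaplan-Meier and Cox analyses. It also lists all bleeding among the follow-up events to be recorded. No section gives a common bleeding window, or censoring of bleeding time at the end of dual therapy.

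**The concern.** An endpoint that compares randomised arms should be counted over the same period in each arm. Here the counting period is the treatment period, and in stable patients the protocol assigns the treatment period by stent type. A transfusion in month 4 is an event for a stable DES patient and is not one for a stable BMS patient.

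Longer dual therapy after DES may well cause more bleeding, and that would be a true consequence of the strategy. The stated definition cannot isolate it, because an excess on DES would appear even if every patient's bleeding risk over the first year were the same. At stake are the two endpoints that set the bleeding cost against the ischaemic results, in the pooled DES versus BMS comparison and in each DES versus BMS. The error always runs against DES.

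**Working it through.** The protocol gives no bleeding rate, power or sample size for these endpoints, so there is no planned figure to reproduce. The check is of the windows, then of the size of the artefact when nothing truly differs.

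**Inputs from the protocol.** Window of 1 month (stable BMS) or 12 months (DES, and BMS with ACS): sections 2, 4 and 6. Enrolment of 3 × 800, hence 800 BMS and 1600 DES: section 9. Fisher's exact test: section 10.

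**Assumptions, not in the protocol.** True 12-month major bleeding r = 3% in every patient of either arm. Stable share s = 30%, 50% or 70%. Share of first-year bleeds falling in month 1, f = 1/12 (even spread), 40% or 60%.

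**Step 1, windows.** Stable patients: 1 month versus 12, ratio 12. ACS patients: 12 versus 12, ratio 1. Mean BMS window = s × 1 + (1 − s) × 12 months:
- s = 30%: 0.3 + 8.4 = 8.7 months; 12/8.7 = 1.38
- s = 50%: 0.5 + 6.0 = 6.5 months; 12/6.5 = 1.85
- s = 70%: 0.7 + 3.6 = 4.3 months; 12/4.3 = 2.79

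**Step 2, counted bleeding with no true difference.** DES = r. BMS = (1 − s)r + s·f·r. Example with s = 50%, f = 1/12: 0.5 × 3% + 0.5 × 3%/12 = 1.5% + 0.125% = 1.63%, against 3.0% on DES. The last column is the exact probability that Fisher's two-sided test gives p ≤ 0.05 at 800 versus 1600.

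| f | s | BMS counted | DES counted | Ratio | Falsely significant |
|---|---|---|---|---|---|
| 1/12 | 30% | 2.18% | 3.0% | 1.38 | 19% |
| 1/12 | 50% | 1.63% | 3.0% | 1.85 | 52% |
| 1/12 | 70% | 1.08% | 3.0% | 2.79 | 88% |
| 40% | 30% | 2.46% | 3.0% | 1.22 | 10% |
| 40% | 50% | 2.10% | 3.0% | 1.43 | 22% |
| 40% | 70% | 1.74% | 3.0% | 1.72 | 44% |
| 60% | 30% | 2.64% | 3.0% | 1.14 | 7% |
| 60% | 50% | 2.40% | 3.0% | 1.25 | 12% |
| 60% | 70% | 2.16% | 3.0% | 1.39 | 20% |

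The ratio does not depend on r; the false-significance rate does. Over the same grid it runs from about 6% to 69% at r = 2%, and from about 9% to 98% at r = 5%.

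**Step 3, net clinical benefit.** Assume 6% primary events in both arms, independent of bleeding, with s = 50% and r = 3%. Event rate = 1 − 0.94 × (1 − counted bleeding).
- DES: 1 − 0.94 × 0.970 = 8.8%
- BMS, f = 1/12: 1 − 0.94 × 0.98375 = 7.5%; falsely significant about 18%
- BMS, f = 40%: 1 − 0.94 × 0.979 = 8.0%; about 10%
- BMS, f = 60%: 1 − 0.94 × 0.976 = 8.3%; about 7%

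**Step 4, common window.** With one window for everyone, both arms are counted at r and the ratio is 1.0 under the same assumptions.

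**The case against.** **The twelve-month phrase may have meant a fixed window.** It is possible that a common 12 months was intended, or that an analysis plan not at hand fixes the rule. As written, though, the twelve months is a cap and the therapy is the window, and no section supports the other reading. If a fixed window was meant, the text should say so.

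**The time-to-event analysis may cope.** If bleeding time were censored at the end of dual therapy, a log-rank test under an even bleeding hazard would reject at about its nominal rate (about 4.5% in simulation). The protocol does not state that censoring, Fisher's test remains the planned comparison of proportions, and such an analysis would answer an on-drug question rather than compare the two strategies.

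**Bleeding clusters early.** All patients receive a loading dose and undergo a procedure, so an even spread probably overstates the artefact. This stands, and is why the table runs to 60% in month 1. The artefact shrinks but keeps its direction.

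**Only secondary endpoints are touched.** This also stands. The primary endpoint, its sample size and the randomisation are unaffected. Among the aims, bleeding and net clinical benefit are named only in aim E, where XienceV is compared under 12 months of either thienopyridine.

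Two stronger readings are tempting.
- A reader might infer that bleeding data are themselves missing in stable BMS patients, because Appendix 2 says "AEs will be collected for all patients from first dose of protocol treatment until 30 days after the last dose of treatment". The documents do not support this. Section 10 records all bleeding during follow-up, Appendix 2 gives serious adverse events no end date tied to the therapy, and bleeds needing surgery or transfusion would ordinarily be serious.
- A reader might also infer that historical aim D is biased in the same way. Its planned durations do differ, but aim D does not name bleeding, and section 10 makes historical net-benefit comparisons descriptive only.

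**Conclusion.** The point holds for the randomised BMS versus DES comparisons of major bleeding and net clinical benefit: pooled, XienceV versus Prokinetik, and Nobori versus Prokinetik. It acts through stable patients alone. ACS patients, XienceV versus Nobori, and aim E have equal planned windows.

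That the windows are unequal follows from the protocol's text. How much this matters rests on assumed bleeding rates, timing and case mix. At 3% bleeding the spurious ratio is about 1.1 to 2.8 and false significance about 7% to 88%, a wide range in which no single value deserves emphasis. For net clinical benefit, with half the patients stable, false significance is about 10% to 18% for month-1 shares of 40% down to 1/12, and about 7% at 60%. The pairwise contrasts at 800 versus 800 were not sized; their ratios are the same.

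It would be too strong to say that this undermines the trial's main safety conclusion, which rests on cardiac death/MI at 24 months in all arms. It should be fixed as a defect of secondary endpoints.

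**What to change.** In section 8 and the synopsis, define the bleeding endpoint as all adjudicated major non-CABG bleeds from randomisation to one fixed time, for example 12 months, in every patient, whether on or off dual therapy. State that net clinical benefit uses that same bleeding window in all arms. Report bleeding during dual therapy, per patient-time, as a supplement.

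The cost is a change of wording. Section 10 already records all bleeding, so no new data item is needed, and neither the treatment durations nor the Appendix 2 adverse-event window has to change. The drawback is that bleeds occurring off therapy dilute the pure drug effect, which the supplementary table covers. The change should be made before results by arm are known, since afterwards it could look data-driven.

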## 9. Sample Size calculation

In the 558 patients of BASKET/BASKET-LATE with treatment of large native vessels, cardiac deaths and non-fatal MIs were seen in 6% of BMS compared to 11.2% of DES treated patients ( $p=0.05$ ) after a follow-up of 18 months. Based on a slightly more conservative assumption (i.e. 6.0 vs. 10.5% after follow-up of 24 months) and on the design of the proposed study, a total of 753 patients for the BMS group and a total of 1506 patients for the DES group (which includes the XienceV® and Nobori® groups) would have to be included to reject the null hypothesis that the event rates for the DES and BMS groups are equal at an alpha level=0.05 in a two-tailed test with probability of more than 90% (power). In view of an expected withdrawal rate of 5-6% and the 2:1 randomization, we plan to enroll 3x800 patients into the study or a total of 2400 patients; i.e. we could still detect a relative difference of 22% between BMS and DES at an alpha level of .027 with a power of 70% if the BMS rate stays the same, and with a slighter higher power an an alpha level of .05 if the BMS rate would be 5.5% instead of 6%. To address the second aim (comparison of BMS with each of the two DES) within BASKET-PROVE II, the sample size of 800 patients per stent group will allow to reject the null hypotheses that the event rates for each of the DES and the BMS are equal at an alpha level of 0.027 in a two-tailed test with a power of 80%. A simulation showed that a nominal alpha of 0.027 is appropriate to adjust for the duplicity of testing in the following setting: if three groups of equal size are compared with respect to the relative frequency of a certain outcome, the z-standardized differences ( $p_2-p_1$ ) and ( $p_3-p_1$ ) follow a 2-dimensional normal

distribution with variance 1 and covariance 0.5 under the null hypothesis. The Fisher's exact test will be used to evaluate the above hypotheses.

If we assume a total inclusion rate of 170 patients per month as in BASKET-PROVE by all participating centres, we should finish inclusion within 13-15 months. If results of BASKET-PROVE should differ markedly from these assumptions, i.e. difference in rates in cardiac death/MI of BMS patients vs. XienceV® patients <3.0% or >5.0%, then these sample size considerations will have to be reassessed.

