##### **Statistics:**

A sample size of 800 patients/stent type (753 plus compensation for a withdrawal rate of 5 to 6%) would provide a power of more than 90% to detect, at an alpha level of 0.05 in a two

tailed test, a significant difference between the BMS group and the DES group. This sample size will also allow to detect a significant difference between the BMS and each of the DES groups with a power of 80% at an alpha level of 0.027.

Intention to treat analysis: bivariable group comparisons will be first performed, then time to event will be evaluated both by Kaplan Meier statistics and Cox-regression analysis taking into account influential factors.

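### The stated 70% power for a 22% relative BMS–DES difference is wrong as written: the planned 2400 patients give about 15–24%

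*Protocol*

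**What the plan says.** Protocol section 9 (Sample Size calculation) plans on event rates of "6.0 vs. 10.5% after follow-up of 24 months", BMS versus DES. It derives 753 BMS and 1506 DES patients for the pooled comparison "at an alpha level=0.05 in a two-tailed test with probability of more than 90% (power"), and raises this to 3 × 800 = 2400 for 5–6% withdrawal.

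The same sentence then claims sensitivity to something smaller: "we could still detect a relative difference of 22% between BMS and DES at an alpha level of .027 with a power of 70" per cent. The condition is that the event rate on BMS is unchanged. A companion clause adds that this also holds "with a slighter higher power an an alpha level of .05 if the BMS rate would be 5.5% instead of 6" per cent.

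The section goes on to give 0.027 as the nominal level for comparing BMS with each of the two DES separately, as an adjustment for testing twice. It names Fisher's exact test, and it ends with a rule that the sizing is reassessed if the predecessor trial shows a BMS–XienceV difference below 3.0% or above 5.0%.

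**The concern.** The planning assumption of 6.0% versus 10.5% is a 75% relative increase (4.5/6.0). On a base of 6.0%, a 22% relative difference is only 1.3 to 1.7 percentage points, about a third of the planned 4.5 points. Power should therefore fall from above 90% to far less than 70%, the more so at the stricter level of 0.027.

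The endpoint is cardiac death or MI, and this sentence is the section's explicit power figure for an effect smaller than the planned one. A reader would take the risk of missing a 22% difference to be 30%. If the figure is wrong, that reader is misinformed about what a non-significant result could exclude. The choice of 0.027 also leaves it unclear which comparison the sentence describes.

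**Working it through.** **Inputs (Protocol section 9).** BMS 6.0% (5.5% in the companion clause); DES:BMS 2:1; 800/1600 enrolled or 753/1506 evaluable; two-sided alpha 0.05 (pooled) or 0.027 (as in the disputed sentence).

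**Formula.** Two-proportion z-test, with p1 = BMS and p2 = DES:

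- p̄ = (n1·p1 + n2·p2)/(n1 + n2)
- s0 = √[p̄(1 − p̄)(1/n1 + 1/n2)]
- s1 = √[p1(1 − p1)/n1 + p2(1 − p2)/n2]
- Power = Φ[(|p2 − p1| − z·s0)/s1], with z = 1.960 at 0.05 and 2.212 at 0.027

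**Step 1: the section's other claims reproduce.**

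- Pooled, 6.0% vs 10.5%, 753/1506, alpha 0.05: p̄ = 0.0900, s0 = 0.01277, s1 = 0.01172. (0.0450 − 1.960 × 0.01277)/0.01172 = 1.70, so power is 95.6% (stated: more than 90%).
- Pairwise, same rates, alpha 0.027: 85.6% with 800 per arm and 83.3% with 753 per arm (stated: 80%).

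**Step 2: the 22% claim at BMS 6.0%, alpha 0.027, 800/1600.** The text does not fix the base or direction of the 22%, so all three versions are shown.

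| 22% taken as | DES rate | (difference − z·s0)/s1 | Power 800/1600 | Power 753/1506 |
|---|---|---|---|---|
| DES 22% above BMS (6.0 × 1.22) | 7.32% | (0.0132 − 2.212 × 0.01096)/0.01063 = −1.04 | 15% | 14% |
| DES 22% below BMS (6.0 × 0.78) | 4.68% | (0.0132 − 2.212 × 0.00954)/0.00992 = −0.80 | 21% | 20% |
| BMS 22% below DES (6.0/0.78) | 7.69% | (0.0169 − 2.212 × 0.01114)/0.01072 = −0.72 | 24% | 22% |

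Simulated Fisher's exact power with 800/1600 is about 14.0%, 19.5% and 23.0%, so the choice of test does not explain the gap. A one-sided test at 0.027 would give 23–34%.

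**Step 3: the companion clause, BMS 5.5%, alpha 0.05, 800/1600.** DES 6.71%: 20%. DES 4.29%: 27%. DES 7.05%: 30%. The claim was slightly more than 70%.

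**Step 4: what the design can detect (BMS 6.0%, higher DES rate).**

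| Comparison | Alpha | Patients | 70% power at DES | 90% power at DES |
|---|---|---|---|---|
| Pooled | 0.027 | 800/1600 | 9.2% (+3.2 points, 53% relative) | – |
| Pooled | 0.027 | 753/1506 | 9.3% (+3.3 points, 55% relative) | – |
| Pooled | 0.05 | 753/1506 | 9.0% (+3.0 points) | 9.9% (+3.9 points) |
| Pairwise | 0.027 | 800/800 | 9.7% | – |
| Pairwise | 0.027 | 753/753 | 9.8% | – |

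At alpha 0.05 with 753/1506, power for the three 22% versions is 21% (7.32%), 28% (4.68%) and 31% (7.69%). Reaching 70% for a 22% difference at alpha 0.027 would need about 4081, 3178 or 2558 BMS patients respectively, each with twice as many DES patients.

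**The case against.** The strongest reply is that the sentence is mis-worded, not miscalculated. It follows directly on 6.0% versus 10.5% and says the trial could still detect something. It may have meant that the assumed excess could shrink by 22%: 4.5 × 0.78 = 3.51 points, or 6.0% versus 9.51%. Power at 0.027 is then 78% (800/1600), 75% (753/1506), 66% (800 per arm) or 63% (753 per arm). Shrinking the 75% relative excess by 22% in the companion clause (5.5% versus 8.72%, alpha 0.05) gives 82%, 79% and 71% for the first three of these sizes, each a little above its partner, as the text says. This brings both clauses much nearer the stated figures than any literal reading does. But the sentence speaks of a 22% difference between BMS and DES, not of a difference that is 22% smaller, and none of the planned sizes gives 70%. One variant of this reading does give 70.0%, but it needs a one-sided test, 753 per arm and a continuity correction. That contradicts the two-tailed test and the 2:1 pooled comparison. Mis-wording is plausible, and the sentence would need correcting in that case too.

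The second reply is that nothing hangs on the sentence. This largely stands. The 2400 comes from 753/1506 plus withdrawal. The synopsis repeats only the claims that reproduce. The reassessment rule would apply if the predecessor trial showed a BMS–XienceV difference below 3.0 points, and 22% relative is 1.3–1.7 points. The rule also fits the true sensitivity: 6.0% versus 9.0% has 71% power with 753/1506 at alpha 0.05. It therefore softens any argument that a null result would be over-read.

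A reader might infer that the trial is underpowered for its primary comparison, or that 0.027 is itself an error. The documents support neither: the main sizing reproduces with room to spare, and the section gives a reason for 0.027 in the two pairwise tests.

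**Conclusion.** The sensitivity statement is wrong as written. For a 22% relative difference between BMS and pooled DES at a BMS rate of 6.0% and two-sided alpha 0.027, power is about 15–24% with 800/1600, against a stated 70%: an overstatement of roughly three- to five-fold. The companion clause is out by a similar amount. The sentence also attaches 0.027 to the pooled comparison, for which the section sets 0.05.

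This rests on the unchanged BMS rate being the planned 6.0%, on a two-sided test as stated, and on 2:1 allocation. The range covers every base and direction for the 22% that the wording allows. The error is confined to this one sentence: the sample size, the primary test and the pairwise claim are unaffected.

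**What to change.** Replace the sensitivity sentence in section 9, including its 5.5% clause, with wording such as:

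> With 753 BMS and 1506 DES evaluable patients, a BMS rate of 6.0% and two-sided alpha 0.05, the pooled comparison has 70% power for a DES rate of about 9.0% (+3.0 points) and 90% power for about 9.9% (+3.9 points). Power for a 22% relative difference is only about 21–31%.

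Keep 0.027 for the two pairwise comparisons only. If the sentence was meant for those, the authors should say so and restate the detectable difference: 70% power at 6.0% versus about 9.7% with 800 per arm, or about 9.8% with 753 per arm. If a 22% smaller excess was meant, name the two rates, the group sizes and the alpha, and give the power that follows.

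The cost is a wording change in one section and a less favourable stated sensitivity. The sample size does not change.

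### The 0.027 level for each DES versus BMS comparison was calibrated on z-statistics but is paired with Fisher's exact test, and section 10 sets a different multiplicity rule; the cost is about 2 points of power, not validity

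*Protocol*

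**What the plan says.** Protocol section 9 covers the second aim, each DES against the BMS, as follows: "the sample size of 800 patients per stent group will allow to reject the null hypotheses", these being that the two event rates are "equal at an alpha level of 0.027 in a two-tailed test with a power of 80" per cent. The level is justified by "A simulation showed that a nominal alpha of 0.027 is appropriate to adjust for the duplicity of testing". The setting is three equal groups in which the two z-standardized differences from the common control follow a bivariate normal "distribution with variance 1 and covariance 0.5 under the null hypothesis".

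The sentence that follows names the test: "The Fisher's exact test will be used to evaluate the above hypotheses".

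Section 10 (Data handling and Analyses) again names Fisher's exact test for proportions. For comparisons of each DES group with the BMS group it adjusts the p-values by Bonferroni-Holm when proportions are compared. It does not mention 0.027.

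**The concern.** A nominal level calibrated by simulation belongs to the statistic that was simulated. The reason to prefer 0.027 to the Bonferroni value of 0.025 is to recover what Bonferroni wastes by ignoring the correlation from the shared BMS arm. Fisher's test is discrete and conservative at these event counts, so it can give back more than that gain. Section 10 then replaces the fixed level with a step-down rule that starts at 0.025, so the protocol does not settle which threshold decides these comparisons.

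At stake is power for the stent-specific safety comparisons on cardiac death or MI, and a decision rule that is unambiguous before the data are seen.

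**Working it through.** **Inputs, all from section 9 unless noted.** Event rates "6.0 vs. 10.5% after follow-up of 24 months". Evaluable numbers "a total of 753 patients for the BMS group and a total of 1506 patients for the DES group", that is 753 per stent. Enrolment of 800 per stent. Level 0.027 two-sided, correlation 0.5. Holm's first step is 0.05/2 = 0.025 (section 10). The common rates of 6 to 10.5% used for the null are an assumption spanning the planned BMS and DES rates.

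**1. The protocol's own level.** For (Z2, Z3) bivariate normal with correlation 0.5, the family-wise error is 1 − P(|Z2| < c, |Z3| < c). At level 0.027 this is 5.01%. Solving for exactly 5% gives c = 2.212 and p = 0.02696, which rounds to 0.027. The figure is reproduced, for z-statistics.

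**2. Family-wise error with the named test.** Let X be the BMS event count, binomial(n, p) with probability b(x), and let r(x) be the probability that one DES arm with the same rate is declared different given X = x. Then family-wise error = Σ b(x)·[1 − (1 − r(x))²], enumerated exactly. The z-test is z = (p̂_DES − p̂_BMS)/√[p̄(1 − p̄)·2/n], with no continuity correction.

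| n per arm | common rate | Fisher at 0.027 | Fisher at 0.025 | z at 0.027 |
|---|---|---|---|---|
| 753 | 6% | 3.88% | 3.55% | 4.97% |
| 753 | 8% | 3.96% | 3.69% | 5.02% |
| 753 | 10.5% | 4.06% | 3.76% | 4.96% |
| 800 | 6% | 3.90% | 3.53% | 4.96% |
| 800 | 8% | 3.96% | 3.65% | 5.01% |
| 800 | 10.5% | 4.12% | 3.77% | 4.99% |

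The per-comparison error with Fisher at 0.027 is 2.1-2.2%. If the common rate were only 3-4%, its family-wise error would be 3.5-3.7%.

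**3. Power for one comparison at level 0.027.** Power = ΣΣ P(X = x)·P(Y = y)·1{p-value ≤ 0.027}.

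| n per arm | rates | Fisher | z | loss (points) |
|---|---|---|---|---|
| 753 | 6.0 vs 10.5% | 81.5% | 83.9% | 2.4 |
| 800 | 6.0 vs 10.5% | 84.0% | 86.1% | 2.1 |
| 753 | 6 vs 9% | 46.4% | 50.3% | 3.9 |
| 800 | 6 vs 9% | 49.1% | 52.8% | 3.7 |

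At 753 per arm, Fisher at 0.027 (81.5%) has less power than the z-test at plain Bonferroni 0.025 (83.0%), so the gain from the simulation is more than cancelled.

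**4. In patients.** The z-test at 753 per arm is matched by Fisher's test at about 795 on a smoothed power curve (795 − 753 = 42) and at 797-798 by direct enumeration (44-45). Fisher's test reaches 80% power at about 728 per arm.

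**5. Under the section 10 rule.** With step-down from a first level a, the power for comparison A is P(pA ≤ a) + P(a < pA ≤ 0.05 and pB ≤ a). With both DES at 10.5% and 753 per arm:

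- Fisher, Holm (a = 0.025): 85.1%
- z, Holm (a = 0.025): 87.3%
- z, a = 0.027 then 0.05: 87.6%

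If only one DES differs, Fisher at 0.025 gives 80.7%.

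**6. A result on which the tests part.** Take 48/800 BMS and 72/800 DES events. p̄ = 120/1600 = 0.075, SE = √(0.075 × 0.925 × 2/800) = 0.01317, z = 0.03/0.01317 = 2.28, p = 0.0227. Fisher's p is 0.0287. At 0.027 the z-test declares a difference and Fisher's test does not.

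**The case against.** The strongest reply is that nothing printed in the protocol becomes false. Section 9 promises 80% power at 0.027 with 800 per group, and Fisher's test delivers it: 84.0% at 800 and 81.5% at 753, after the full withdrawal allowance. The protocol does not say that the attained family-wise error equals 5%; it calls 0.027 appropriate, and a level that keeps the error below 5% is that. An exact test with guaranteed control is a respectable choice, the comparisons are a secondary aim, and the primary pooled test is hardly touched (95.4% with Fisher against 95.7% with z). Under section 10's Holm rule, power with Fisher is already 85.1% at 753 when both DES are at 10.5%, above the 83.9% of a single z-test at 0.027. All of this stands, and it sets the size of the point.

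It does not remove the point. Compared under the same step-down rule, the z-test still gains about 2 points (87.3 against 85.1%). The two sections also still give different thresholds for the same comparisons.

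Two stronger readings are tempting. A reader might infer that the mismatch invalidates the comparisons or leaves them underpowered; the error lies below 5% and the stated power is met, so neither follows. A reader might also infer that the loss consumes the whole withdrawal allowance of 800 − 753 = 47 per arm. The calculation gives 42-45, and the allowance is not used up, because Fisher's test needs only about 728 evaluable patients per arm for 80% power.

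**Conclusion.** The point holds as a matter of efficiency and consistency. The 0.027 is correct for the statistic it was derived from. With the test named in sections 9 and 10, the family-wise error is about 3.9-4.1% (3.5-3.8% at Holm's first step) instead of the 5.0% that the level implies for z-statistics. The cost is about 2 points of power at 6.0 versus 10.5%, equal to about 42-45 patients per arm, and about 4 points at 6 versus 9%. Sections 9 and 10 also disagree on the multiplicity rule.

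These figures assume equal arms of 753 or 800, binary 24-month outcomes without censoring, and common rates of 6-10.5% under the null. No extra patients are needed and no stated figure has to be withdrawn.

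**What to change.** In both section 9 and section 10, name one test and one multiplicity rule for the DES versus BMS comparisons of proportions. Changing section 9 alone would leave section 10 prescribing Fisher's test with Holm.

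- **Preferred:** the two-sided score (z) test without continuity correction, with the smaller p-value tested at 0.027 (|z| = 2.212) and, if that is significant, the other at 0.05. This keeps both the simulated level and the benefit of Holm's second step (about 87.6% power at 753 per arm if both DES are at 10.5%).
- **If Fisher's test is kept:** repeat the simulation with Fisher's test and print that level in both sections. It will lie slightly below 0.034, because 0.034 gives 5.04-5.14% at rates of 8-10.5%. At 0.033 the enumeration gives 4.7-5.0% for rates of 6-10.5%.

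The section 9 sentence naming Fisher's test covers the pooled comparison as well, so the new wording should say which comparisons it governs.

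The cost is a sentence or two in each section, with no patients and no data collection. The downside of the z-test is approximate error control (4.96-5.02% at rates of 6-10.5%) instead of a guarantee. The change should be made before outcome data by stent are seen, since a later switch of test would look driven by the result.
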